## 2.5 Sample Size Determination

The sample size for this study was based on the primary efficacy measure, the proportion of subjects with mRS score  $\leq 1$  at Day 90 of treatment. According to previous clinical studies (see Protocol Reference 7-12), it is estimated that the proportion of subjects with mRS score  $\leq 1$  on Day 90 of treatment will be 50% in the investigational group and 40% in the control group, taking a two-sided  $\alpha$  of 0.05, a power of 80%, and a randomization ratio of 1:1. After calculation, 388 subjects are required in each group. Considering a 15% dropout rate, 457 subjects are planned to be randomized in each group, with a total sample size of 914.

An interim analysis is scheduled to be performed after approximately 50% of patients complete the visit on Day 90. The purpose of interim analysis is to re-estimate the sample size based on primary efficacy indexes. It is conducted by the Independent Data Monitoring Committee (IDMC) and whether the sample size should be increased or remain unchanged is recommended according to the regulations of the IDMC. The sample size may be increased to 1.5 times the scheduled sample size at most, and won't be reduced. If the sample size is adjusted, the method proposed by Cui et al. 1999 (hereinafter referred to as the CHW method) will be used to control type I errors in the final analysis.

Interim analyses and sample size re-estimation were performed by an Independent Data Monitoring Committee (IDMC) as detailed in Section 4.5 of this plan and in the IDMC charter.

## 2.6 Randomization and Blinding

All eligible subjects will be randomly assigned to the investigational or control group according to the ratio of 1:1. The random number table is generated by the standardized software. The detailed parameter settings are set by the randomization plan.

In this trial, a centralized competitive enrollment randomization method will be used, and subjects will be assigned a "screening number" after signing the informed consent form and before performing study-related tests. Subject screening numbers must not be reused.

After the subjects passed screening, the investigator or designee obtained the information of randomization number and corresponding drug number through the randomization system, and distributed the corresponding study drugs according to the randomization number and drug number.

Randomization will be stratified by:

- Onset time:  $\leq 24$  hours vs  $> 24$  hours;
- Investigational site.

The color, description, and packaging (including batch number and shelf life) of the investigational drug (Y-2 sublingual tablet) and placebo control drug (Y-2 sublingual tablet placebo) were identical. Blinding process was completed by statisticians unrelated to this clinical trial. After blinding, the blinding codes will be sealed in duplicate and stored in the leading site and the sponsor, respectively.

The trial was unblinded just once. After the last subject completes the 90-day follow-up in the whole trial, after blind verification, the data is locked and unblinding is performed, that is, the corresponding group of each subject is identified. For interim analysis, according to IDMC charter, unblinded data will be reviewed centrally by IDMC members and their statistical analysis will be performed by a third party unblinded statistician independent of the study project team to ensure blinding during the conduct of the trial.

When a serious adverse event suspected to be related to the investigational drug occurs during the trial, the principal investigator at the site should report to the sponsor to decide whether to initiate the emergency unblinding procedure. Once the blind was broken emergently, the case was treated as a dropout and medication was stopped if the blind was broken emergently during treatment.

This double-blind trial was invalidated if the total blind codes were leaked or emergency unblinding exceeded 20% during the study.

## **2.7 Modification to the statistical analysis in the protocol**

Not available.

## **3 Analysis Dataset**

At the end of the trial, after data cleaning, the study project team will review the data collected during the trial and delimit the analysis dataset according to the following rules.

- **Full Analysis Set (FAS)**

According to the basic principle of intention-to-treat (Intention-To-Treatment, ITT), all subjects who were randomized were included in the full analysis set. The primary efficacy evaluation for

this study was based on the full analysis set.

Treatment assignment for the Full Analysis Set was based on randomization.

- **Per-Protocol Set (PPS)**

Includes all subjects who completed protocol-specified therapy or who did not substantially violate the protocol. The exact definition of a serious protocol violation will be finalized at the time of data review and may generally include (but is not limited to) the following:

- 1) Significant violation of inclusion criteria, affecting the efficacy evaluation;
- 2) There are treatments that seriously interfere with the efficacy evaluation after inclusion;
- 3) Significant drug regimen violation, total dose intensity < 80%;
- 4) Poor compliance seriously affects the efficacy evaluation;
- 5) Delayed medication for too long during treatment;
- 6) Lack of evaluation of primary efficacy indicators.

The PPS was the secondary analysis dataset for efficacy evaluation, and treatment assignment was based on randomization.

- **Safety Analysis Set (SS)**

Defined as all subjects who were randomized and received at least one dose of trial drug and had one safety evaluation. The safety evaluation for this study was based on the Safety Analysis Set.

The treatment groups of the safety analysis set was based on the drug actually received. For the control group, data analysis will be performed by the investigational group as long as the subjects have received one dose of the test drug.

## **4 Statistical Analysis**

### **4.1 General Principles**

All statistical analyses for this study will be performed using the statistical analysis software SAS version 9.4 or higher. All data collected in Case Report Form (CRF) will be statistically calculated by treatment groups. For continuous variables, the number of subjects with non-missing data, mean, standard deviation, median, minimum, and maximum were calculated and listed. The number of decimal places for the minimum and maximum values will be

consistent with that recorded in the database. Means, medians, and standard deviations will be rounded to one more decimal place than the raw data recorded in the database. For discrete variables, frequencies and percentages were calculated and presented. Percentages will be presented to one decimal place.

#### **4.1.1 Significant Level**

Unless otherwise specified, all efficacy analyses will be statistically tested at a 2-sided significance level  $\alpha = 0.05$  to calculate nominal p values, point estimates of efficacy differences, and 2-sided 95% confidence intervals.

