|  | 
using logistic regression.
 
Similar approaches were used for binary secondary outcomes, including mRS score <math>\leq 2</math> on day 90, NIHSS score <math>\leq 1</math> on day 14, 30, and 90, and safety outcomes on adverse events and treatment related adverse events. For mRS score on day 90, an ordinal logistic regression analysis was performed, with the results presented as common OR and 95% CI, where a common OR in favor of Y-2 sublingual tablet was <math>>1.0</math>. For changes in NIHSS score from baseline to day 14, means with 95% CIs were calculated for each group, and the mean differences with 95% CI between the groups were estimated by generalized linear regression. In addition, a post hoc sensitivity analysis was performed using different approaches to impute missing data on the primary efficacy outcome. Finally, the treatment effects on the primary outcome were analyzed among several prespecified subgroups by including the interaction between treatment and subgroup effect into the logistic regression model.
 
All the tests were 2 sided, and <math>P < 0.05</math> was considered statistically significant. Statistical analyses were performed with use of SAS software, version 9.4 (SAS Institute).
 |

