Unblinding sample size will be re-estimated in the interim analysis. If sample size adjustment occurs, the CHW method will be used to weight the test statistics in the final analysis, and the *P* value of the hypothesis testing will be estimated accordingly for statistical inference.

Similar approaches were used for binary secondary outcomes, including mRS score  $\leq 2$  on day 90, NIHSS score  $\leq 1$  on day 14, 30, and 90, and safety outcomes on adverse events and treatment related adverse events. For mRS score on day 90, an ordinal logistic regression analysis was performed, with the results presented as common OR and 95% CI, where a common OR in favor of Y-2 sublingual tablet was  $>1.0$ . For changes in NIHSS score from baseline to day 14, means with 95% CIs were calculated for each group, and the mean differences with 95% CI between the groups were estimated by generalized linear regression.

In addition, a post hoc sensitivity analysis was performed using different approaches to impute missing data on the primary efficacy outcome. Finally, the treatment effects on the primary outcome were analyzed among several prespecified subgroups by including the interaction between treatment and subgroup effect into the logistic regression model.

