### 2.3 Study Endpoints

- **Primary Efficacy Endpoint**
  - The proportion of patients with mRS score  $\leq 1$  on Day 90 after randomization.
- **Secondary Efficacy Endpoints**

- mRS score on Day 90 of treatment;
  - the proportion of patients achieving a good functional outcome (mRS  $\leq 2$ ) on day 90;
  - the change in NIHSS score from baseline to 14 days.
  - the proportion of patients achieving an NIHSS score  $\leq 1$  on day 14, 30 and 90 days after randomization.
- **Safety Endpoints**

Safety evaluation include:

- adverse events within day 90.
- treatment related adverse events within day 90.
- changes in vital signs and laboratory data before and after treatment.

According to the protocol, exploratory biomarker studies will also be conducted in parallel in this study, and data collection and analysis will be handled separately and not included in this statistical analysis plan.

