#### 4.3.2 Secondary Efficacy Endpoints

Secondary efficacy endpoints were analyzed on the FAS and PPS without imputation of missing values.

- mRS score on Day 90 of treatment

Descriptive statistics were performed by treatment groups on mRS scores at Day 90 of treatment to calculate the number of non-missing subjects, mean, standard deviation, median, minimum, and maximum, and at the same time, the number and percentage of subjects with different mRS scores (including missing values) at Day 90 of treatment were calculated. an ordinal logistic regression analysis was performed, with the results presented as common OR and 95% CI, where a common OR in favor of Y-2 sublingual tablet was  $>1.0$

- Proportion of subjects with mRS score  $\leq 2$  at Day 90 of treatment

Descriptive statistics were performed on the number and percentage of subjects with mRS score  $\leq 2$  at Day 90 of treatment as previously described by treatment groups. Comparisons were made between treatment groups using the same logistic regression model as for the primary analysis.

- NIHSS score change from baseline at Day 14 of treatment

Observed values and changes from baseline in NIHSS score at each visit will be summarized descriptively by treatment groups and the number of non-missing subjects, mean, standard

deviation, median, minimum, and maximum will be calculated. Difference in NIHSS score from baseline to Day 14 was be calculated the means with 95% CIs were calculated for each group, and the mean differences with 95% CI between the groups were estimated by generalized linear regression.

- The proportion of NIHSS score of 0-1 at 14, 30, and 90 days of treatment;

The number and percentage of subjects with NIHSS scores of 0 to 1 at 14, 30, and 90 days of treatment will be calculated by treatment groups. Comparisons were made between treatment groups using the same logistic regression model as for the primary analysis.

- Other Efficacy Measures

Not applicable.

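### Six secondary efficacy comparisons are each tested at two-sided 0.05 with no gate, order or supportive label, and the protocol abstract lets any of them be called statistically significant

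*Combined protocol and SAP*

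**What the plan says.** **Endpoints.** SAP 2.3 names one primary endpoint, the proportion with mRS ≤1 at Day 90. Its four secondary bullets give six comparisons, because the NIHSS 0-1 proportion is taken at three visits:

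1. "mRS score on Day 90 of treatment", analysed by ordinal logistic regression
2. mRS ≤2 at Day 90
3. NIHSS change from baseline to Day 14
4. NIHSS 0-1 at Day 14
5. NIHSS 0-1 at Day 30
6. NIHSS 0-1 at Day 90

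**Level.** SAP 4.1.1: "Unless otherwise specified, all efficacy analyses will be statistically tested at a 2-sided significance level" of 0.05. The sentence goes on to give the purpose: "to calculate nominal p values, point estimates of efficacy differences, and 2-sided 95% confidence intervals".

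**Secondary analyses.** SAP 4.3.2: "Secondary efficacy endpoints were analyzed on the FAS and PPS without imputation of missing values". It names a model or estimate for each endpoint, but no testing order, alpha split or condition on the primary. Protocol 8.4 is equally silent: "Similar approaches were used for binary secondary outcomes".

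**Decision wording.** The statistical analysis part of the protocol abstract ends: "All the tests were 2 sided, and P < 0.05 was considered statistically significant". SAP 2.7 records no change to the protocol's analysis.

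**Rule for concluding efficacy.** SAP 4.3.1 gives one, for the primary only: the lower 95% limit of the odds ratio must exceed 1, with the main reading on the FAS.

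**The concern.** The two documents give the secondary p values different standing. Under the abstract, any of the six with P<0.05 is statistically significant, whatever the primary shows. Under SAP 4.1.1 the p values are nominal. That word covers all efficacy analyses, the primary included, so it does not set the secondaries apart as non-confirmatory.

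If the abstract's rule is followed, a secondary can be declared significant after a failed primary, and six tests give six chances of it. A reader of the results could not tell from the plan whether such a finding was error-controlled. The CHW correction does not help: protocol 8.6 and SAP 4.5.1 apply it to the primary test after a sample-size change, and SAP 4.5 records that the sample size was not increased.

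**Working it through.** **The plan's own figure.** The documents state no family-wise error rate for the secondaries. The nearest figure is the sample size, which shows where the 0.05 is spent. With 50% versus 40%, two-sided 0.05, 80% power, 1:1 allocation and pooled variance:

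n = (1.960·√(2·0.45·0.55) + 0.842·√(0.25 + 0.24))² / 0.10² = 387.3, so 388 per group; 388/0.85 = 456.5, so 457.

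Both match SAP 2.5. The full 0.05 goes to the primary.

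**Inputs for the secondaries.** Six comparisons (SAP 2.3, 4.3.2), each two-sided at 0.05 (SAP 4.1.1), so |z| > 1.960. The correlation among the test statistics is not in the documents. I assume a common value ρ and vary it from 0 to 0.9.

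**Step 1: at least one P<0.05 among the six, either direction, all six nulls true.**

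Independent: 1 − 0.95⁶ = 0.265. The sum bound for any dependence is 6 × 0.05 = 0.30.

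Correlated: write each statistic as √ρ·X + √(1−ρ)·e, with X and the e independent standard normal. Then the rate is 1 − E[p(X)⁶], where p(X) = Φ((1.960 − √ρX)/√(1−ρ)) − Φ((−1.960 − √ρX)/√(1−ρ)), integrated numerically over X.

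**Step 2: at least one secondary significant in favour of Y-2, with the primary not favourably significant.** Add the primary as a seventh statistic with the same ρ and all seven nulls true. With q(X) = Φ((1.960 − √ρX)/√(1−ρ)), the probability is E[(1 − q(X)⁶)·q(X)]. At ρ = 0 this is (1 − 0.975⁶) × 0.975 = 0.141 × 0.975 = 0.137.

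| Assumed ρ | Step 1: any of six, either direction | Step 2: favours Y-2, primary not favourably significant |
|---|---|---|
| 0 | 26.5% | 13.7% |
| 0.3 | 24.1% | 11.2% |
| 0.5 | 20.7% | 9.0% |
| 0.7 | 16.4% | 6.4% |
| 0.9 | 10.8% | 3.2% |

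**Step 3: does equal correlation matter?** Ordinal mRS and mRS ≤2 come from the same Day-90 score, so their correlation should be higher than most. I simulated an illustrative unequal structure with assumed correlations from 0.35 to 0.8, the highest between those two endpoints (1,000,000 draws). It gives 19.7% for Step 1, within the equal-correlation range.

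**The case against.** The case on the other side has real weight.

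- **The SAP already says nominal** and pairs its p values with estimates and confidence intervals, which is most of what a supportive label would require. This stands in part. The word applies to the primary as well, and SAP 2.7 does not withdraw the abstract's significance sentence.
- **Only the primary has an efficacy rule.** SAP 4.3.1 ties the conclusion of better efficacy to the primary odds ratio, and SAP 4.3.2 gives no success criterion for any secondary. This stands and lowers the severity.
- **The significance wording is one generic sentence in the abstract.** It is absent from protocol 8.4 and from SAP 4.1.1 and 4.3.2. True, but it covers all tests and is the only place that says what P<0.05 means.
- **The two-direction rate does not measure the stated harm.** Also right. The harm is a favourable secondary alongside a failed primary, and Step 2 is the figure for that. At ρ = 0.5 it is less than half the Step 1 figure.

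A reader might go further in three ways, none of which the documents support. One is to quote about 21% as the plan's false-positive rate; that figure needs a common correlation near 0.5, which appears nowhere. Another is that the trial's efficacy conclusion carries this error; the primary is a single test with its own rule. The third is that repeating the analyses on the PPS raises the rate by a known amount; the documents give no basis for quantifying it.

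**Conclusion.** The point holds as an unresolved labelling and multiplicity gap in the secondary endpoints. Six comparisons are each tested at two-sided 0.05 with no gate, order or label, and the abstract's significance rule conflicts with the SAP's nominal p values. The primary's type I error is unaffected.

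With all six nulls true, the chance of at least one significant secondary is 10.8% to 26.5% for ρ from 0.9 to 0, or 2.2 to 5.3 times a single test's 5%. With the primary null also true, the chance of a Y-2-favourable secondary beside a primary that is not favourably significant is about 3% to 14%. The sizes rest on normal test statistics, true nulls and an assumed common correlation; the wording conflict rests on none of these. I rate it a cheap improvement.

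**What to change.** 1. In the protocol abstract, restrict the P<0.05 sentence to the FAS analysis of the primary endpoint.
2. In SAP 4.1.1 and 4.3.2, state that the six secondary comparisons are supportive and will be reported as estimates with 95% confidence intervals and nominal p values, with no claim of statistical significance.
3. If a confirmatory secondary claim is wanted, test on the FAS only, and only after a significant primary. Use a fixed order set before unblinding, each test at two-sided 0.05, stopping at the first non-significant result. The order in SAP 2.3 is one option, but the documents do not say that it reflects priority.

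The cost is a few lines of wording, with no new data, patients or analyses. The downside is that an isolated secondary with P<0.05 could no longer be claimed as significant. Timing limits the third item. The minutes of the third IDMC meeting (25 December 2022) record completed follow-up of all 914 patients and agreement to lock the database. An order chosen after results are seen controls nothing, so once the trial is unblinded only items 1 and 2 remain useful.

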#### **4.1.2 Estimation of Missing Values**

Missing values were not imputed except for the primary efficacy measure. Missing value imputation methods for the primary efficacy measure are detailed in Text Section 4.3.1.

#### **4.1.3 Data Arrangement**

**1) Wrong grouping convention:** Following conventions will be made for the cases with wrong drug used during the trial:

- FAS: In case of any inconsistency between randomization and drug grouping, randomization shall prevail
- PPS set: Randomization inconsistent with drug use will be excluded.
- SS set: Statistical analysis will be performed according to actual drug group when randomization is inconsistent with drug grouping.

**2) Missing dates:** If previous dates are incomplete and affect subsequent date calculations, impute as follows if there is no conflict with other dates:

- Date associated with adverse event
  - Day, Month, and Year of event onset date are all missing: do not impute, date is missing;
  - Missing day and month of AE onset date: If the year of onset date is the same as the year of first dose date, fill in as first dose date; if the year of onset date is not the same as the year of first dose date, fill in as January 1.
  - Date of AE onset is only missing for day: If the date of AE onset is same as the date of first dose, fill as the date of first dose; if the date of AE onset is different from

---

month and year, fill as day 1.

- Date of AE end is missing: Date of end is not imputed and will be considered missing.
- Missing day and month of stop date in adverse event: end date imputed as 31 December.
- End date in Adverse Event is only missing for Day: Impute as last day of month.
- Dates associated with concomitant medications
  - Day, Month, and Year of start of concomitant medication are all missing: do not impute, date is missing;
  - Missing day and month of concomitant medication start date: If the year of start date is the same as the year of first medication date, fill in as first medication date; if the year of start date is not the same as the year of first medication date, fill in as January 1.
  - Concomitant medication start date is missing only for Day: If "Month and Year" of start date are the same as "Month and Year" of first medication date, fill in as first medication date; if "Month and Year" of start date are not the same as "Month and Year" of first medication date, fill in as day 1.
  - Date of end of concomitant medication is missing: End date is not imputed and agreed as continuous use.
  - Day and month of concomitant medication end date are missing: end date is imputed as 31 December.
  - Concomitant medication end date is only missing for Day: Impute as last day of month.
  - Date of first dose appointment: Date of start of treatment period

Dates in the data listings were listed as completed on the eCRF.

- 3) Definition of baseline: The last non-missing data before the first dose is baseline. If a subject took trial medication but did not have a date of first dose, the last non-missing data prior to the date of enrollment was taken as baseline.
- 4) Change from baseline was defined as: test value at post-treatment follow-up – baseline test value.

**5) Data derivation and transformation:**

- Age: Year is used as unit, = (date of informed consent – date of birth)/365.25, rounded.
- Time from treatment to onset = time of first dose – time of stroke onset in hours (h) rounded to one decimal place.
- Stroke onset time is defined as the time at which the patient 's symptoms begin, and if it starts during sleep, the time at which the last manifestation is normal should be used as the time of onset. If stroke onset time is completely missing, impute with 0h0m on day of onset; if only minutes are missing, impute with 0m.
- Estimated glomerular filtration rate (eGFR):
- $eGFR (ml/min/1.73m^2) = 186 * (Scr/88.4)^{-1.154} * (age)^{-0.203} * 0.742$  (if female) \* 1.233

Where Scr is serum creatinine (umol/L), age is age, and female is female.

Renal function: normal renal function (baseline eGFR  $\geq$  90), mild renal impairment ( $60 \leq$  baseline eGFR < 90), and moderate to severe renal impairment (baseline e GFR < 60).

